### Participants

#### Participant eligibility

Participants must be (1) age 18 or older; (2) speak English, Spanish, or Cantonese; (3) have a UCSF Health or SFHN PCP; (4) be willing to use a smartphone (iOS or Android – either their own or one provided by the study); (5) have chronic, non-malignant pain for at least 3 months; and (6) be willing to participate in a 12-month patient-centered CP management study where they will be randomized into one of two comparison arms. Spanish and Cantonese languages were chosen in addition to English due to their high prevalence in the San Francisco Bay Area. Any individuals with conditions that prevent informed consent (e.g., dementia, active psychosis) and patients with chronic pain-related surgery scheduled in the next 12 months will be excluded. Patients will not be excluded if they have a current SUD, mood disorder, or anxiety disorder. Participants are allowed to participate in other concomitant pain management interventions, including procedural interventions (e.g., joint injections), during the 12-month study but are asked to report these treatments. Pharmacotherapy interventions (e.g., opioids) are not assessed due to patient concerns voiced during the intervention development phase regarding potential unwanted changes to their medication regimen that could result from study participation.

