#### Participant randomization

We will randomize at the level of the patient. While this poses a modest risk of provider contamination between intervention and control participants, providers will not receive any communication from the study team after enrollment. We have further addressed the potential effect of contamination by increasing sample size, allowing detection of smaller intervention effects.

Participants will be stratified by 4 demographic groups (Cantonese-speaking, Spanish-speaking, Black/African American English-speaking, and multi-cultural English-speaking) and randomly assigned 1:1 to either the INSPIRE intervention (Group 1) or control groups (Group 2). The CRC will utilize random block randomization to maximize balance between treatment groups throughout accrual while ensuring the randomization sequence remains unpredictable. A random allocation sequence was generated using a computer, where treatment groups were labeled as Group 1 or 2. After participants consent to study participation and complete baseline measures, clinical research coordinators will assign the next available study ID number in sequence, identify the allocated group, and inform participants of their assignment. The study ID number and Personal Health Information (PHI) will be stored in a HIPAA-compliant manner (REDCap) along with the intervention assignment (Group 1 or 2). Study personnel responsible for outcome evaluations will be blinded to which Group 1 or 2 represents.

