### General statistical considerations

Participants’ demographic characteristics (i.e., age, sex, race/ethnicity, socioeconomic status, marriage status) and clinical characteristics at baseline and follow-up will be summarized by intervention groups (INSPIRE vs. control) as well as by sex and language groups to assess potential differences in sex and language groups. Boxplots and other appropriate plots will be used to assess the balance of baseline characteristics between the two groups. The distributions of outcome measures will be checked by histograms and other appropriate plots for the selection of appropriate analysis methods and potential data transformation. Graphs of outcomes over time will be used to determine an appropriate way to model the time effect.

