### Primary analysis of the primary endpoint

Our primary analyses will assess the intention-to-treat (ITT) effect of INSPIRE on PEG score compared to the control group at 3 months. The ITT approach will include all the randomized participants, including non-adherers and dropouts, in the analyses. A linear mixed effects model (LMM) will evaluate the group difference over time in change in PEG scores. The models will include the stratification variable (language), group (INSPIRE vs. control), time, and time*group interaction as fixed effects, and random intercept and slope for the nested three-level random effects controlling for correlation due to clustering by clinics, providers, and participants. Baseline demographics and characteristics will be balanced between the two groups by randomization; if any baseline covariates are identified as imbalanced, these will also be included in models. Time will be included in the LMM in an appropriate way (linear, categorical, quadratic, or two pieces) based on the graph of the outcome over time. The time*group interaction will provide the estimated ITT effect of INSPIRE compared to control over time, where the contrast between the INSPIRE and control groups at 3 months is our primary interest, using a significance level of 0.05. The LMM adopts a less stringent assumption on missingness (i.e., missing at random) than complete case approaches (missing completely at random) and will include all available data from all the randomized participants in the analysis.

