### Secondary analyses of the primary outcome

Secondary analyses of PEG scores will supplement the primary analysis, including (1) a modified intention-to-treat (mITT) analysis will be performed using the same LMM as the primary analysis but excluding randomized participants who do not participate and drop out after Week 0 and those who do not have chronic pain or have PEG<4 and drop out by Week 1; (2) using an independent *t* test to test corresponding contrasts from the same LMM as the primary analysis to assess if PEG score would be different between the treatment groups at 6 and 12 m; (3) using potential outcome-based approaches to estimate the INSPIRE effects while accounting for nonadherence to intervention [121]; (4) assessing if there are any baseline covariates associated with dropouts and performing sensitivity analyses to see how much the results will change after including covariates associated with dropouts in the models, using multiple imputation, or considering pattern mixture models; and (5) exploring potential heterogeneous effects by demographics or characteristics with sub group analyses. Given the discovery feature of those secondary analyses, a significance level of 0.05 will be used to avoid missing potentially important findings, which will be verified in future studies.

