### Analysis of secondary endpoints

Secondary analyses will evaluate the ITT effects of the INSPIRE intervention on physical functioning, QOL, sleep, depression, anxiety, and global satisfaction with treatment with generalized linear mixed effects models (GLMM) like those used for the primary analysis. These GLMM will include language, time, treatment group, time*treatment in fixed effects while controlling correlations by clustering (clinics, providers, and participants). The time*treatment will assess if the secondary outcome changes over time differ by treatment groups. Holm’s step-down procedure will be used to adjust for multiple comparisons in secondary analyses [122].

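### Randomisation uses four strata, but the primary and secondary models name language, which has three levels and pools the two English-speaking strata

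*Protocol article*

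**What the plan says.** The section Participant randomization defines the strata: "Participants will be stratified by 4 demographic groups (Cantonese-speaking, Spanish-speaking, Black/African American English-speaking, and multi-cultural English-speaking". Within them, participants are "randomly assigned 1:1 to either the INSPIRE intervention (Group 1) or control groups (Group 2". The factor therefore has four levels, and the English speakers are divided in two.

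The section Primary analysis of the primary endpoint describes the linear mixed model for PEG: "The models will include the stratification variable (language), group (INSPIRE vs. control), time, and time*group interaction as fixed effects". The modified intention-to-treat analysis is run "using the same LMM as the primary analysis but excluding randomized participants who do not participate", and the 6- and 12-month contrasts come from that model too, so both inherit the term.

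For the secondary endpoints: "These GLMM will include language, time, treatment group, time*treatment in fixed effects". General statistical considerations summarises participants by arm "as well as by sex and language groups".

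Participant eligibility requires that participants "speak English, Spanish, or Cantonese", which gives language three levels. Nowhere does the article name the four-level stratum as a model term or as a reporting group.

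**The concern.** The protocol makes two statements about the same variable that cannot both hold. It stratifies on four groups, then labels the stratification variable with a factor that can take only three values. An analyst coding from the analysis section would fit three levels and lose the boundary between the two English-speaking strata.

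Two things are at stake. The first is precision: stratification balances the arms within each stratum, and a model that omits part of the stratification cannot credit that balance, so its standard error may be larger than it need be. The second is reporting. The Discussion says that consistent recruitment, retention and outcomes across populations would validate the cultural and linguistic adaptation. Summaries by language alone cannot show this for Black/African American participants, because they are pooled with all other English speakers.

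**Working it through.** **1. Levels.** Randomisation: Cantonese-speaking, Spanish-speaking, Black/African American English-speaking, multi-cultural English-speaking = 4 levels. Language: English, Spanish, Cantonese = 3 levels. One boundary is lost.

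**2. Inputs.** From the sample size section: 586 enrolled, 73% retention, effect size 0.3, two-sided 5% level. Completers per arm are 293 × 0.73 = 213.89. The enrolment figure is taken as given; it was based on a two-sample t-test and does not depend on this model term. The documents give neither the mean PEG gap between the two English strata nor their shares. Both are therefore assumed: a gap g of 0.3 to 0.8 SD (within-stratum SD = 1), with g = 1.0 as an extreme, and each English stratum at 25% of the sample.

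**3. Difference between arms at 3 months, no baseline adjustment.** Pooling two equal strata whose means differ by g adds (g/2)² to the variance among English speakers. They are half the sample, so the residual variance rises by

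v = 0.5 × (g/2)²

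and the model standard error is multiplied by √(1 + v). The treatment estimate keeps its true sampling variability, so a larger standard error makes the test conservative:

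- type I error = 2 × [1 − Φ(1.96 × √(1 + v))]
- power = Φ(λ − 1.96 × √(1 + v)), with λ = 0.3/√(2/213.89) = 3.102

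| g (SD) | v | SE ratio | Type I error | Power |
|---|---|---|---|---|
| 0 (or four-level model) | 0 | 1.000 | 0.050 | 0.873 |
| 0.3 | 0.011 | 1.006 | 0.049 | 0.871 |
| 0.5 | 0.031 | 1.016 | 0.047 | 0.867 |
| 0.8 | 0.080 | 1.039 | 0.042 | 0.857 |
| 1.0 | 0.125 | 1.061 | 0.038 | 0.847 |

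Simulation (5,000 runs per setting, 107 completers in each of four strata) agrees. The mean estimate for a true effect of 0.3 lay between 0.298 and 0.302 under both models, so there is no bias. At g = 1.0 the mean standard error was 0.1026 with language and 0.0966 with the stratum, a ratio of 1.062. If each English stratum is only 12.5% of the sample, v is halved.

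**4. Change from baseline through time-by-group.** A stratum difference that is constant over time sits in the participant intercept and drops out of a within-person change. The model used for the check has a random participant intercept, categorical time and an assumed within-person correlation of 0.5. With complete data, the ratio of standard errors (language to stratum) for the 3-month interaction is 1.0000 at g = 0.3, 0.5 and 0.8. With 73% retention, a small simulation gave 1.0001, 1.0005 and 1.0011. A generalised least squares calculation in which the missing 27% contribute baseline only gave 1.0004, 1.0011 and 1.0027. Either way the inflation is below 0.3%.

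**5. Which contrast applies.** The primary analysis section models change in PEG and takes the treatment effect from the time-by-group interaction, which points to step 4. It also names the contrast between the groups at 3 months as the primary interest, which leaves step 3 open.

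**The case against.** The strongest reply is that the protocol does commit to including the stratification variable, so the intent to match the randomisation is stated and only the label in brackets is incomplete. Language may simply be shorthand for the four groups. This is possible, but the article never says so, and it uses the bare word again for the secondary endpoints. The point concerns a term that the article states, so it is not a detail left to an analysis plan.

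The reply is right that the numerical consequence is slight. Under the change-from-baseline reading it is almost nothing. Clinic effects, or adjustment for baseline pain, would also absorb part of any stratum difference under the other reading.

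A reader might infer three stronger things, none of which the documents support:

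- **That the Black/African American stratum gets no summary or effect estimate.** Race/ethnicity is among the characteristics summarised by arm, and the secondary analyses of PEG include exploratory subgroup analyses by demographics. A stratum main effect in the primary model would in any case give no stratum-specific treatment effect; that takes a subgroup or interaction analysis.
- **That every model adjusts for language alone.** The Abstract lists baseline pain, anxiety and physical function as covariates. The primary analysis section adds that "if any baseline covariates are identified as imbalanced, these will also be included in models". The mediation models refer to relevant baseline covariates and name neither language nor stratum.
- **That the treatment effect is biased or the type I error inflated.** Neither occurs. Any distortion is towards conservatism.

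**Conclusion.** The mismatch is real: four strata in the randomisation, a three-level term in the primary model, the analyses that reuse it and the secondary-endpoint models. It is a mislabelled model term, not a threat to validity. For an unadjusted 3-month contrast the standard error is about 0.6% to 4% too large, and power falls by 0.2 to 1.7 percentage points (0.873 to between 0.871 and 0.857). These figures rest on the assumed 25% shares and a gap of 0.3 to 0.8 SD, neither of which the documents supply. For a change-from-baseline contrast the effect is close to nil. The reporting consequence is limited to the by-group summaries, which as written do not separate Black/African American participants from other English speakers. The point is minor in size, but worth correcting because the correction is practically free.

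**What to change.** In Primary analysis of the primary endpoint and in Analysis of secondary endpoints, replace language with the four-level randomisation stratum, listing the four groups as in Participant randomization. The modified intention-to-treat analysis and the later PEG contrasts then follow automatically. In General statistical considerations, give the by-group summaries for the same four strata, so that the consistency across populations invoked in the Discussion can be examined for Black/African American participants. If language was meant as shorthand for the four groups, one sentence saying so corrects the model sections.

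The cost is a change of wording and one further fixed-effect parameter (three instead of two for the factor), negligible with about 428 expected completers (586 × 0.73). No sample size or power figure in the protocol has to change. The correction should be documented before the comparative analysis of outcomes.

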#### INSPIRE intervention: health coaches

This innovative intervention element will include a one-hour orientation/introduction to the program followed by 12 weekly telehealth coaching calls to patients guided by PRO scores and module completion data summarized in the coach’s dashboard. One-hour booster sessions will be delivered at months 5 and 11. The exact roles and expectations of the coaches were determined by current best practices of multiculturally validated programs, patient preferences, and provider/clinic/system needs, with all duties and procedures summarized in a detailed coaching manual [74, 109–115]. We anticipate one PhD-level clinician will serve as the lead coach that supervises 4–5 additional coaches using the UCSF coaching model with a digital patient registry and online dashboard to track participant progress [116].

Coaches will utilize a manual to standardize content facilitation for each week’s materials. Coaches take notes, help patients establish goals, follow their progress, and problem solve issues around intervention engagement and adherence. Coaches were trained for over 80 hours using didactics, role plays, and video review with feedback and remediation when necessary. Coaches will direct participants to their PCP regarding medications, referrals to specialty care, and to address urgent medical issues, and will report AE’s to the study PI and coordinator.

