### Sample size justification

The sample size calculation was based on the primary analysis comparing the primary outcome (PEG scores) between the INSPIRE and control groups at 3 months. Based on the literature, we expect to observe an effect size of 0.3 in PEG score at 3 months [57, 58, 60, 70, 119, 120]. With a power of 0.8 and Type I error of 0.05 in a two-sided independent t-test, assuming 73% retention, a sample size of 586 (293/group) is needed at the enrollment to identify such an effect size at 3 months.

Although we will use Holm’s step-down procedure to adjust for multiple comparisons in secondary analyses, we will take a conservative approach in the power calculation for secondary analyses using Bonferroni with an individual Type I error of 0.01 to control for the family-wise Type I error in 5 comparisons on secondary outcomes. The sample size of 586 (293/group) at the enrollment will provide a power of 0.8 to detect an effect size of 0.366 (a group difference of 0.366*SD) in secondary outcomes between the INSPIRE and control groups. We consider the detectable effect sizes realistic that we expect to observe in the study. With a less conservative Holm’s step-down approach than Bonferroni that we will use in actual secondary analyses to adjust for multiple comparisons, the planned sample size will detect a smaller effect size than 0.366 with a power of 0.80 for secondary outcomes. Adverse events, severe adverse events, and unanticipated problems during the study will be summarized with frequencies and percentages and compared between the treatment groups using Fisher’s exact test or Chi-squared test as appropriate.

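### The primary model has no term for coach, although 5–6 coaches treat the INSPIRE arm only; if coaches differ in effect, the standard error of the 3-month contrast is too small

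*Protocol article*

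**What the plan says.** Under Primary analysis of the primary endpoint, the protocol fits a linear mixed model with fixed effects for language, group, time and time by group, and "random intercept and slope for the nested three-level random effects controlling for correlation due to clustering by clinics, providers, and participants". The 3-month contrast from the time-by-group term is tested at 0.05. Analysis of secondary endpoints names the same three clustering levels. None of the supplementary analyses listed under Secondary analyses of the primary outcome involves coach.

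On delivery, INSPIRE intervention: health coaches states: "We anticipate one PhD-level clinician will serve as the lead coach that supervises 4–5 additional coaches". Each INSPIRE participant has an assigned coach (Study onboarding), who gives an orientation and 12 weekly calls before month 3. Controls receive a manual and one orientation visit and do not work with a coach (Waitlist control condition).

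The provider level does not cover coaches. Participant randomization says that "providers will not receive any communication from the study team after enrollment", so providers are the patients' own clinicians, whereas coaches are trained and supervised by the study.

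The sample size rests on an independent t-test: "With a power of 0.8 and Type I error of 0.05 in a two-sided independent t-test, assuming 73% retention, a sample size of 586".

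**The concern.** Patients are randomised individually, so clinics and providers span both arms and largely cancel from the treatment contrast. Coaches do not. Participants who share a coach share whatever that coach does better or worse than the others, and this happens in one arm only. The design is partially nested, and the model leaves out the one source of correlation that treatment itself creates.

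Where that correlation is positive, the model treats the INSPIRE mean as more precise than it is. The confidence interval for the 3-month PEG difference is then too narrow and the primary test rejects too often. The t-test power calculation makes the same assumption of no coach clustering.

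**Working it through.** **Inputs from the protocol.** Effect size 0.3 ("we expect to observe an effect size of 0.3 in PEG score at 3 months"), two-sided alpha 0.05, power 0.80, retention 73%, 293 enrolled per arm, one lead plus 4–5 coaches.

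**The plan's own sample size.** n per arm = 2(1.96 + 0.842)² / 0.3² = 174.4, so 175; an exact t calculation gives 176. Dividing by 0.73 gives 240–242 per arm, or 480–484 in total, not the stated 586. Retention of 60% gives 292–294 per arm (584–588), which does match 586. The statement that this sample "will provide a power of 0.8 to detect an effect size of 0.366" at alpha 0.01 needs 175–177 per arm, and 293 × 0.60 = 175.8. That mismatch is a separate matter, but it leaves two plausible analysed sizes: 293 × 0.73 = 214 per arm (power 0.87) or 176 per arm (power 0.80). Both are carried forward.

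**Assumption.** The coach ICC is not in the documents. The range 0.01–0.05 is assumed, with zero as the reference.

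**Formulas.** With m = analysed per arm / number of coaches:
- design effect in the INSPIRE arm: DE = 1 + (m − 1) × ICC
- variance ratio of the arm difference: R = (DE + 1) / 2, as only one arm is clustered
- true SE / reported SE = √R
- true type I error = 2(1 − Φ(1.96 / √R))

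**Example.** 214 analysed, 5 coaches, ICC 0.02: m = 42.8; DE = 1 + 41.8 × 0.02 = 1.836; R = 1.418; √R = 1.191; type I error = 2(1 − Φ(1.646)) = 0.100.

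**Results (SE ratio / type I error):**

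| Analysed per arm, coaches (m) | ICC 0.01 | ICC 0.02 | ICC 0.05 |
|---|---|---|---|
| 214, 5 (42.8) | 1.10 / 7.5% | 1.19 / 10.0% | 1.43 / 17.1% |
| 214, 6 (35.7) | 1.08 / 7.0% | 1.16 / 9.1% | 1.37 / 15.1% |
| 176, 5 (35.2) | 1.08 / 7.0% | 1.16 / 9.1% | 1.36 / 15.0% |
| 176, 6 (29.3) | 1.07 / 6.7% | 1.13 / 8.4% | 1.31 / 13.4% |

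At ICC 0, R = 1 and the error stays at 5%. If the lead coach only supervises and four coaches treat, the range is 7.5%–19.7%.

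**Simulation check.** With 20,000 trials per cell, 214 per arm and coach effects in one arm only, the test without coach rejected in about 7%, 9%–10% and 15%–17% of null trials at ICC 0.01, 0.02 and 0.05, and in about 5% at ICC 0. Across both sizes, a coach-level Satterthwaite test held 5.1%–5.8%.

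**Power for 0.3 SD once coach variance is counted** (normal approximation, before small-sample degrees of freedom): at 214 per arm, 0.87 falls to 0.81–0.82, 0.74–0.76 and 0.58–0.62 at ICC 0.01, 0.02 and 0.05. At 176 per arm, 0.80 falls to 0.74–0.75, 0.68–0.70 and 0.54–0.58.

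**Where the coach effect must act.** Baseline PEG is measured before assignment, so a coach cannot affect it, and the test is a change contrast. A simulation of that contrast at ICC 0.05 with 6 coaches rejected in 4.7% of null trials when the coach effect was constant over visits, and in 16.6% when it acted only after baseline. The post-baseline effect is the one that matters.

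**The case against.** **The inflation is conditional.** It needs coaches who truly differ in effect and a conclusion meant for coaches beyond this team. If the programme does nothing through any coach, the error stays at 5%. If the target is the effect as delivered by these coaches, omitting coach is defensible. The protocol does not name its target, although its Discussion looks to scaling the intervention to other populations and settings. This objection stands, and it sets the strength of the point.

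**The ICC is assumed.** A coaching manual, lead-coach supervision, about 80 hours of training, an 80% rubric pass mark, review of 5% of sessions and shared app modules may all reduce differences between coaches. None shows that they are zero, but the upper end of the range is less secure for it. The arithmetic is also a two-sample comparison at 3 months, not the full longitudinal model.

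**Five or six coaches estimate a variance poorly.** At ICC 0.01–0.02 a moment estimate of the coach variance is zero or negative in about 28%–43% of trials. This favours a sensitivity analysis over a change to the primary model.

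**The separate analysis plan may cover it.** That plan is not at hand. But the article lists its clustering levels explicitly for both primary and secondary models, so this is a stated specification.

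**Arguments that do not help.** The booster sessions at months 5 and 11 come after the primary endpoint. The language term is shared by both arms, so it does not remove a coach effect confined to one. The number of visits available for random slopes has no bearing on the coach omission.

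**Conclusion.** The omission is real, and its consequence is conditional. The stated models cover clinic, provider and participant, and leave out the only clustering that treatment induces. With a coach ICC of 0.01–0.05, 5–6 coaches and 176–214 analysed per arm, the reported standard error of the 3-month contrast is too small by a factor of about 1.07–1.43, and the type I error is about 7%–17%.

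A reader might infer that the primary test's error rate is above 5% as planned. The documents do not support that: they give no coach ICC, and at zero there is no inflation. A reader might also infer that the surplus in the sample size, if 73% retention holds, settles the matter. It would roughly absorb the power loss at an ICC of 0.01, but it does not correct the error rate: with a fixed number of coaches, more participants per coach increase the inflation.

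**What to change.** 1. Record the coach assigned to each INSPIRE participant in the analysis data. Assignment already happens at onboarding, but the protocol does not say that it is kept as a variable.
2. Pre-specify a named sensitivity analysis of the 3-month contrast that adds a coach random effect active only in the INSPIRE arm and only after baseline (coach by post-baseline time), with Satterthwaite or Kenward-Roger degrees of freedom. Do not use a constant coach intercept: it would leave the standard error essentially unchanged and reassure falsely.
3. Report the coach variance or ICC, including when it is estimated at zero.
4. State in the sample size section that the t-test power assumes no coach clustering.

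The work is analysis-plan wording and one variable. The statistical cost is a wider interval in that analysis, possibly much lower power at larger ICCs, and an imprecise coach variance. Fixing this before unblinded data are seen avoids a later choice between two p-values.

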**Methods:**

The Integrating Nonpharmacologic Strategies for Pain with Inclusion, Respect, and Equity (INSPIRE) study evaluates a blend of these non-pharmacologic, evidence-based interventions using a pragmatic, parallel, two-arm RCT comparing intervention participants with wait-list controls. The INSPIRE intervention includes a 12-week curriculum delivered via a multilingual mobile app paired with weekly telehealth coaching. The primary outcome will be the “Pain, Enjoyment, and General Activity (PEG)” scores at 3 months. Secondary outcomes include PEG scores at 6 and 12 months, physical functioning, quality of life, sleep, depression, anxiety, and global satisfaction with treatment at 3, 6, and 12 months. Primary mediators to be examined include pain cognitions and health behaviors. Secondary mediators may include stigma and isolation, trust in healthcare providers, and both engagement and satisfaction with the INSPIRE intervention. The intention-to-treat primary analysis will be conducted with covariates including baseline measures of pain, anxiety, and physical function.

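### The Abstract and the Methods state different covariate sets for the primary analysis, and the Methods add covariates according to observed baseline imbalance

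*Protocol article*

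**What the plan says.** The protocol article describes the primary model in two places.

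- **Abstract, Methods paragraph:** "The intention-to-treat primary analysis will be conducted with covariates including baseline measures of pain, anxiety, and physical function". No condition is attached.
- **Primary analysis of the primary endpoint:** "The models will include the stratification variable (language), group (INSPIRE vs. control), time, and time*group interaction as fixed effects", with random effects for clinic, provider and participant. Baseline pain, anxiety and physical function are not named. Other baseline variables enter by a rule: "if any baseline covariates are identified as imbalanced, these will also be included in models".

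The section General statistical considerations says how balance will be judged: "Boxplots and other appropriate plots will be used to assess the balance of baseline characteristics between the two groups". The article gives no threshold and no list of candidate variables.

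On the role of baseline PEG, the primary analysis section says "A linear mixed effects model (LMM) will evaluate the group difference over time in change in PEG scores". It takes the time-by-group interaction as the effect of the intervention, and adds that "the contrast between the INSPIRE and control groups at 3 months is our primary interest, using a significance level of 0.05".

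**The concern.** A confirmatory trial needs one primary model, fixed before the outcome data are seen. Here an analyst working from the Abstract and one working from the Methods would fit different models and report different estimates and p-values. The two agree only if pain, anxiety and physical function all happen to be judged imbalanced.

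The imbalance rule is a poor way to choose covariates. The Methods themselves rely on randomisation to balance the groups, so any imbalance that remains is chance. What makes a covariate worth including is how strongly it predicts the outcome. A rule based on imbalance can admit a variable unrelated to PEG and leave out a strong predictor that happens to be balanced. Because balance is read from plots, the choice also rests on judgement made after the baseline data are in.

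The handling of baseline PEG is unsettled too. If baseline PEG is a repeated response and each group has its own baseline mean, the group difference at 3 months is essentially the raw difference, while the interaction is the difference in change. These are two different statistics, and the text points to both.

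**Working it through.** **1. The plan's own figure.** Inputs from Sample size justification: "we expect to observe an effect size of 0.3 in PEG score at 3 months", and "With a power of 0.8 and Type I error of 0.05 in a two-sided independent t-test, assuming 73% retention". The normal formula gives 2 × (1.960 + 0.842)² / 0.3² = 174.4, so 175 completers per arm; the t-test gives 176. Dividing by 0.73 gives 242 per arm, 484 in total. The article states 586 (293 per arm), so its figure is not reproduced. It matches 60% retention instead: 293 × 0.60 = 175.8. That discrepancy is a separate matter. It matters here only because it leaves two possible completer counts:

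- 293 × 0.73 = 213.9, taken as 214 per arm;
- 176 per arm, the number the t-test requires.

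**2. Precision of the three possible contrasts.** Let r be the correlation between baseline and 3-month PEG. The article gives none, so 0.4 to 0.6 is assumed. In SD units, with equal SDs at both times, complete data and no clustering:

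- raw 3-month difference: SE = √(2/n)
- difference in change: SE = √(2(1 − r) × 2/n)
- baseline PEG adjusted: SE = √((1 − r²) × 2/n)

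Since 1 − r² = (1 − r)(1 + r), it is never larger than 1 or than 2(1 − r). The adjusted contrast is therefore never less precise than either alternative.

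Power is Φ(0.3/SE − 1.96). For example, at n = 214 the raw SE is √(2/214) = 0.0967, and Φ(3.10 − 1.96) = 0.874.

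| Completers per arm | Contrast | r = 0.4 | r = 0.5 | r = 0.6 |
|---|---|---|---|---|
| 214 | raw 3-month score | 0.874 | 0.874 | 0.874 |
| 214 | change | 0.809 | 0.874 | 0.934 |
| 214 | baseline PEG adjusted | 0.923 | 0.948 | 0.973 |
| 176 | raw 3-month score | 0.804 | 0.804 | 0.804 |
| 176 | change | 0.729 | 0.804 | 0.882 |
| 176 | baseline PEG adjusted | 0.867 | 0.901 | 0.940 |

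**3. What the imbalance rule does.** It was simulated at 214 per arm, with 5,000 runs per setting. The article gives no threshold, so p < 0.05 was assumed. There were six candidate covariates. Baseline PEG, anxiety and physical function were correlated 0.4 with each other, and correlated r, 0.3 and 0.3 with the outcome. Three further variables were correlated 0.1 with the outcome.

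- About 25% of trials added at least one covariate.
- Type I error under the rule was 0.039 to 0.045 at a nominal 0.05, which is slightly conservative.
- Power under the rule was 0.89 to 0.90 on 3-month scores and 0.82 to 0.93 on change.
- Power with baseline PEG, anxiety and physical function prespecified was 0.93 to 0.97.

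**The case against.** The strongest defence has four parts.

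- **The article is a condensation.** It says a statistical analysis plan was developed, and that plan is not shown. A threshold, a candidate list or the coding of baseline PEG could properly sit there. This is fair, and their absence is not the point. What remains is that the article itself makes two incompatible statements about one analysis and states the imbalance rule outright.
- **Power may be adequate anyway.** The trial is sized on an unadjusted t-test, and at 214 completers per arm the raw score already gives 0.87. So omitting covariates does not by itself break the design assumption. The precision given up is still real at either completer count.
- **Analysts are blinded.** The Blinding section says so, and this limits discretion. It does so only in part, because the Participant randomization section of the same article identifies Group 1 as INSPIRE.
- **No error inflation is shown.** This stands. Applied mechanically, the rule was slightly conservative in the simulation.

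Some stronger readings are tempting but not supported:

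- *A reader might infer that the Methods forgo baseline adjustment altogether.* On the natural reading baseline PEG is part of the outcome vector, so the time-by-group interaction nets it out. What is given up is the more efficient use of baseline PEG and any default adjustment for anxiety and physical function.
- *A reader might infer that participants without follow-up fall out of the model.* That requires change from baseline to be the response, whereas the section says all available data from all randomised participants are used.
- *A reader might calculate that some covariate is very likely to be flagged.* With about 25 candidates, 1 − 0.95^25 = 0.72. But this assumes a p < 0.05 rule and independent variables. The article states no such rule, and pain, mood, sleep and function scores are unlikely to be independent.

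**Conclusion.** The concern holds in a limited form. The article gives two incompatible covariate sets for the primary analysis. The set in the Methods depends partly on the data, and the section leaves open which 3-month contrast is meant. The consequences are an estimate that depends on the analyst and avoidable loss of precision. They are not a demonstrated failure of validity.

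At 214 completers per arm and 0.3 SD, power is 0.87 on the raw score or 0.81 to 0.93 on change, against 0.92 to 0.97 with baseline PEG adjusted. At 176 per arm, 0.80 on the raw score rises to 0.87 to 0.94. These figures rest on an assumed correlation of 0.4 to 0.6 and on a two-time-point calculation without clustering. The ranking of the three contrasts follows from the algebra and does not depend on the correlation chosen. The contradiction and the imbalance rule are on the page and need no assumption.

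**What to change.** Reconcile the Abstract with the section Primary analysis of the primary endpoint, and fix the covariates there in advance:

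1. Name baseline GAD-7 and baseline PROMIS physical function as covariates, as the Abstract already implies.
2. Add the randomisation stratum with the four levels given under Participant randomization, in place of language, which would merge the two English-speaking strata. The Abstract does not mention the stratum; it belongs in the model because allocation was stratified on it.
3. Use baseline PEG once. The preferred form models the PEG score, not change, at 0, 3, 6 and 12 months, with group means constrained equal at baseline. This has essentially the precision of a baseline covariate and keeps all randomised participants in the model. Entering baseline PEG as a covariate with 3, 6 and 12 months as responses is workable, but participants with no follow-up then contribute nothing.
4. State the single 3-month contrast from that model that will be tested.
5. Delete the imbalance rule from the primary model. Report balance descriptively, and keep any imbalance-driven adjustment as a labelled sensitivity analysis.

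The cost is wording in the protocol and analysis plan, dated and settled before unblinding. Table 1 already schedules PEG, GAD-7 and PROMIS physical function at baseline, so no new data are needed.
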